## Abstract

**Objective::**

Patients with acute respiratory failure often require mechanical ventilation to reduce the work of breathing and improve gas exchange; however, this may exacerbate lung injury. Protective ventilation strategies, characterized by low tidal volumes (≤ 8mL/kg of predicted body weight) and limited plateau pressure below 30cmH_2_O, have shown improved outcomes in patients with acute respiratory distress syndrome. However, in the transition to spontaneous ventilation, it can be challenging to maintain tidal volume within protective levels, and it is unclear whether low tidal volumes during spontaneous ventilation impact patient outcomes. We developed a study protocol to estimate the prevalence of low tidal volume ventilation in the first 24 hours of spontaneous ventilation in patients with hypoxemic acute respiratory failure and its association with ventilator-free days and survival.

**Methods::**

We designed a multicenter, multinational, cohort study with a 28-day follow-up that will include patients with acute respiratory failure, defined as a partial oxygen pressure/fraction of inspired oxygen ratio < 300mmHg, in transition to spontaneous ventilation in intensive care units in Latin America.

**Results::**

We plan to include 422 patients in ten countries. The primary outcomes are the prevalence of low tidal volume in the first 24 hours of spontaneous ventilation and ventilator-free days on day 28. The secondary outcomes are intensive care unit and hospital mortality, incidence of asynchrony and return to controlled ventilation and sedation.

**Conclusion::**

In this study, we will assess the prevalence of low tidal volume during spontaneous ventilation and its association with clinical outcomes, which can inform clinical practice and future clinical trials.

## INTRODUCTION

Patients with acute respiratory failure (ARF) generally require the use of mechanical ventilation (MV) to reduce the work of breathing and maintain adequate gas exchange. However, experimental and clinical studies have demonstrated that MV can contribute to worsening lung injury.^(1,2)^ Clinical trials have shown that the use of protective ventilation, which consists of using tidal volumes (V_T_) equal to or less than 8mL/kg of predicted body weight (PBW) and limiting airway plateau pressure below 30cmH_2_O, is associated with better clinical results and reduced mortality in patients with acute respiratory distress syndrome (ARDS).^(3–7)^

In the initial phase of MV, patients are frequently ventilated in assisted-controlled modes, in which tight control of V_T_ and/or airway plateau pressure is more easily implemented. However, controlled ventilation usually requires sedation and sometimes the use of neuromuscular blockers.^(8,9)^ Previous studies have shown that the use of controlled ventilation is associated with reduced diaphragmatic muscle mass with consequent muscle weakness.^(10–13)^ Conversely, overload of the respiratory muscles during the acute phase of respiratory failure can cause fatigue and is associated with respiratory muscle injury.^(14)^

One way to avoid these two extremes is to use assisted ventilation modes in which the patient's spontaneous inspiratory efforts are supported by the ventilator, avoiding disuse of the respiratory muscles,^(10–12)^ without generating fatigue, since the patient is supported by the ventilator during inspiration.

However, the management of the patient's inspiratory effort presents an important clinical challenge, as patients with acute lung injury may have high levels of respiratory drive, which can result in high V_T_ and/or patient ventilator asynchrony. The development of strategies to regulate respiratory drive may allow a safe compromise between the benefits and risks of spontaneous breathing during MV.^(15)^

Despite the strong scientific evidence supporting protective ventilation, several studies have identified low adherence to it and found significant barriers to the implementation of a protective ventilation strategy in patients with ARF and ARDS.^(16–18)^ A large observational study that included patients in 50 countries revealed an association between low V_T_ and better survival^(19)^ but low adherence to low V_T_. This study was performed before the coronavirus disease 2019 (COVID-19) pandemic, which mobilized the world to manage a large number of ventilated patients, which might have increased the knowledge of how to manage patients with ARDS under MV. Clinical guidelines recommend protective ventilation for COVID-19 patients, and studies conducted during the pandemic have shown greater adherence to the use of low V_T_ during controlled MV and an association with better survival.^(20,21)^ However, observational studies conducted in COVID-19 and non-COVID-19 patients have evaluated adherence to protective ventilatory strategies in the early days of MV, during which patients are typically in assist-control ventilatory modes. To what extent adherence to protective ventilatory parameters occurs during spontaneous ventilation remains unknown. Moreover, it is unknown how much ventilatory practices changed in the aftermath of the COVID-19 pandemic.

There are no studies evaluating the use of low V_T_ for spontaneous ventilation in patients with ARF in Latin America. This study aims to assess the prevalence of low V_T_ ventilation implementation in the first 24 hours of spontaneous ventilation in intensive care units (ICUs) in Latin America and its association with important clinical outcomes.

## METHODS

### Study design and location

This multicenter, multinational, cohort study protocol will include patients with ARF transitioning to spontaneous ventilation in ICUs in Latin American countries.

We will invite investigators from ICUs in ten Latin American countries. Invitations will be sent to all ICUs in the Brazilian Research in Intensive Care Network (BRICNet) and Latin American Intensive Care Network (LIVEN) databases by email, and we have identified one investigator in each of the countries to serve as a national coordinator responsible for using a snowball strategy to invite ICUs and support the local investigators with regulatory and logistic issues.

### Objectives and outcomes

The primary objectives are to estimate the prevalence of low V_T_ ventilation (V_T_ < 8mL/kg of PBW) in the first 24 hours of spontaneous ventilation in patients with hypoxemic ARF and its association with ventilator-free days on day 28. Tidal volume will be assessed five times over the first 24 hours after the transition to spontaneous ventilation to account for potential variation. To determine whether V_T_ was below or above 8 mL/kg of PBW for a given patient, we will calculate the weighted average V_T_ based on the duration of each evaluation period. Accordingly, the first assessment, collected one hour after the transition, carries a weight of 1/24, the second assessment, collected 5 hours after (and 6 hours after the transition), carries a weight of 5/24, and the third, fourth and fifth assessments, collected after 12 hours, 18 hours and 24 hours of the transition, respectively, will each carry a weight of 6/24.

The secondary objectives are to estimate the association between the rate of adherence to low V_T_ ventilation in spontaneous ventilation and survival, estimate the incidence of asynchrony in the first 24 hours after the transition to spontaneous ventilation and associated mortality, estimate the proportion of patients who returned to sedation and controlled MV in the first 24 hours or at any time after the transition to spontaneous ventilation, assess the adherence to low positive end-expiratory pressure (PEEP) by fraction of inspired oxygen (FiO_2_) table in the first 24 hours after the transition to spontaneous ventilation, and identify barriers associated with nonadherence to low V_T_ ventilation during spontaneous ventilation.

### Eligibility criteria

We will screen all patients admitted to the participating ICUs under MV and include patients who meet the eligibility criteria (Figure 1).

**Figure 1 f1:**
[figure not shown]
Study flow diagram.

The inclusion and exclusion criteria are described in table 1.

**Table 1 t1:** Participant inclusion and exclusion criteria

Inclusion criteria
• Age > 18 years.
• Patients with hypoxemic ARF, defined as a PaO_2_/FiO_2_ ratio ≤ 300mmHg, under controlled invasive MV, with an expected duration of MV of at least 24 hours.
• Patients transitioned to spontaneous ventilation (PSV, PAV Plus, NAVA, CPAP and APRV).
**Exclusion criteria**
• Tracheostomized patients.
• Decision not to maintain or add life support measures on the day of assessment (palliative care).
• Patients in ECMO.
• Patients with an air fistula or barotrauma that prevents adequate tidal volume monitoring.
• Severe injuries to the central nervous system that result in abolished or very high respiratory drive, for whom it is not possible to maintain a protective tidal volume.

ARF - acute respiratory failure; PaO_2_/FiO_2_ - partial oxygen pressure/fraction of inspired oxygen; MV - mechanical ventilation; PSV - pressure support ventilation; PAV - proportional assist ventilation; NAVA - neurally adjusted ventilatory assist; CPAP - continuous positive airway pressure; APRV - airway pressure release ventilation; ECMO - extracorporeal membrane oxygenation.

### Sample size calculation

There are no previous studies that have estimated the rate of adherence to low V_T_ in patients with spontaneous ventilation; therefore, we used a conservative approach. To estimate the prevalence with a confidence limit of 5% precision, an anticipated adherence of 50%, and up to 10% loss to follow-up, we estimated that we need to include 422 patients. Additionally, we calculated the power to detect a 3 day difference in ventilator-free days with a standard deviation of 9 days,^(22)^ and we anticipate a statistical power of at least 80% even with a loss to follow-up rate of 10%, provided that the prevalence is between 25 and 75%.

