### Statistical plan analysis

We will perform descriptive statistics, using the mean and standard deviation for continuous variables that present a normal distribution, the median and interquartile ranges for continuous variables that do not present a normal distribution and proportions for categorical variables.

Differences between patients receiving V_T_ less than or equal to 8mL/kg of PBW and patients receiving greater than 8mL/kg of PBW in the first 24 hours after transition to spontaneous ventilation will be evaluated using t tests, Mann–Whitney tests or chi–square tests, according to patient characteristics and data distribution.

The prevalence of adherence to low V_T_ ventilation in spontaneous ventilation during the initial 24 hours (V_T_ less than 8mL/kg of PBW), proportion of asynchrony in the first 24 hours after the transition to spontaneous ventilation, proportion of patients who return to sedation and controlled MV in the first 24 hours or at any time after the transition to spontaneous ventilation and adherence to a low PEEP/FiO_2_ table in the first 24 hours after the transition to spontaneous ventilation will be presented, along with the respective 95% confidence intervals.

Possible barriers associated with nonadherence (V_T_ during the initial 24 hours of spontaneous ventilation less than 8mL/kg of PBW) will be analyzed using a logistic regression model.

To characterize hospital survival at 28 days based on V_T_ during the initial 24 hours of spontaneous ventilation, we will employ the Cox proportional hazards model and generate Kaplan–Meier curves. We will analyze mortality within 28 days using the V_T_ during the initial 24 hours of spontaneous ventilation and according to the incidence of asynchrony during the first 24 hours after the transition to spontaneous ventilation using mixed logistic regressions with the center treated as a random effect.

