The comparison of V_T_ during the initial 24 hours of spontaneous ventilation (less than 8mL/kg of PBW versus greater than 8mL/kg) in relation to ventilator-free days within 28 days will be performed using mixed generalized regression models considering the distribution that best fits the data, incorporating center as a random effect. We constructed a conceptual causal diagram in the format of a directed acyclic graph (DAG),^(24)^ including the association between V_T_ during the first 24 hours of spontaneous ventilation and ventilator-free days at 28 days and the most relevant variables (Figure 1S - Supplementary Material): body mass index (BMI) and SAPS 3 at baseline, SOFA on the day before transition, PaO_2_/FiO_2_ at the moment of the ARF diagnosis, and PEEP, RASS, and pH one hour before transition.

All analyses will be performed using the R statistical program (R Core Team; Vienna, Austria; https://www.R-project.org), and we will consider p < 0.05 to indicate statistical significance.

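### The 422 patients behind the 5-point precision for the primary prevalence assume independent patients, although patients are clustered in ICUs and the plan models centre for other outcomes

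*Protocol article*

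**What the plan says.** The sample size section of the protocol article gives three inputs: "To estimate the prevalence with a confidence limit of 5% precision, an anticipated adherence of 50%, and up to 10% loss to follow-up". From these, "we estimated that we need to include 422 patients". It mentions no design effect, ICC, number of ICUs or patients per ICU.

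The study design section makes the ICU the recruiting unit: "We will invite investigators from ICUs in ten Latin American countries". The eligibility section then has every ventilated patient in those ICUs screened.

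In the statistical section, the prevalence of low tidal volume and the other proportions (asynchrony, return to sedation and controlled ventilation, adherence to the PEEP/FiO2 table) "will be presented, along with the respective 95% confidence intervals". The type of interval is not stated. In the same section the ventilator-free-days model is fitted "incorporating center as a random effect", and the 28-day mortality models likewise treat centre as random.

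**The concern.** The prevalence of low tidal volume is a primary outcome, and 5 points is the only precision the article promises for it. Tidal volume during assisted breathing depends partly on how a unit sets support and sedation, so two patients in one ICU are likely to be more alike than two patients in different ICUs. The discussion itself expects practice to vary between regions. Positive correlation within ICUs means that 422 patients carry less information about the overall prevalence than 422 independent patients would.

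The plan accepts centre correlation for ventilator-free days and mortality but gives it no allowance when it sizes the study for a measure of care delivery. At stake are a headline precision that the design may not support and, depending on the interval method chosen, the coverage of the reported interval.

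**Working it through.** **Inputs from the article.** Half-width d = 0.05, prevalence p = 0.50 and loss 10% (sample size section). Confidence level 95%, so z = 1.96 (statistical section; the sample size section does not give a level).

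**Reproducing 422.** n = z²p(1−p)/d² = 1.96² × 0.25 / 0.05² = 384.16. Then 384 × 1.1 = 422.4. The three stated inputs account for the whole of 422, so the implied design effect is 1.

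**Precision with no clustering.** Half-width = 1.96 × √(0.25/N).
- All 422 analysed: 4.77 points.
- After 10% loss, 422 × 0.9 ≈ 380 analysed: 5.03 points. Multiplying by 1.1 does not quite restore 384 after a 10% loss; dividing by 0.9 gives 384.16/0.9 = 426.8.

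**Largest design effect that still gives 5 points at p = 50%.** 422/384.16 = 1.10 and 380/384.16 = 0.99. With 380 analysed there is therefore no room for any positive ICC.

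**Precision with clustering.** Design effect DE = 1 + (m − 1) × ICC, with m patients per ICU and equal-sized ICUs; half-width = 1.96 × √(0.25 × DE/N). Both m and ICC are assumptions, since the article gives neither.

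| m per ICU | ICC | DE | Half-width, N = 380 | Half-width, N = 422 |
|---|---|---|---|---|
| 4 | 0.01 | 1.03 | 5.10 | 4.84 |
| 4 | 0.05 | 1.15 | 5.39 | 5.12 |
| 10 | 0.01 | 1.09 | 5.25 | 4.98 |
| 10 | 0.05 | 1.45 | 6.05 | 5.74 |
| 10 | 0.10 | 1.90 | 6.93 | 6.58 |
| 20 | 0.05 | 1.95 | 7.02 | 6.66 |
| 20 | 0.10 | 2.90 | 8.56 | 8.12 |

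**Coverage if a plain binomial interval were used.** Approximate coverage = 2Φ(1.96/√DE) − 1. Take 380 patients in 40 equal ICUs, so m = 9.5.
- ICC 0.05: DE = 1 + 8.5 × 0.05 = 1.425, coverage about 90%.
- ICC 0.10: DE = 1 + 8.5 × 0.10 = 1.85, coverage about 85%.

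Unequal ICUs lower this further. With DE = 1 + ((1 + CV²)m − 1) × ICC and an assumed coefficient of variation of ICU size of 0.8, (1 + 0.64) × 9.5 − 1 = 14.58. DE is then 1.73 and 2.46, and coverage about 86% and 79%.

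**Prevalence away from 50%.** With 380 analysed, the design effect that still gives 5 points is 380 × 0.05²/(1.96² × p(1−p)): about 1.18 at p = 30% and 1.32 at p = 25%.

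**The case against.** Three arguments on the other side have weight.

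First, a reader might infer that the reported 95% intervals will be too narrow. The article does not support that. It names no interval method, and the method may be set in an analysis plan that is not shown. Undercoverage follows only if a plain binomial interval is used; an ICU-clustered interval would be valid, only wider. This objection stands in full.

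Second, a reader might infer that 5 points is certain to be missed. That too goes beyond the article. Tidal volume is recorded at the bedside in the first 24 hours, whereas loss to follow-up mainly concerns later outcomes, so the prevalence denominator may be nearer 422 than 380. In that case a design effect up to 1.10 is absorbed: at 10 patients per ICU and ICC 0.01 the half-width is 4.98. The 50% is also a deliberately cautious choice, and a true prevalence of 25 to 30% would absorb a modest design effect. Many small ICUs would keep the loss slight. This makes the size of the shortfall conditional. It does not rescue the statement on the inputs the plan chose for itself, and an unseen plan cannot supply a missing allowance, because the stated inputs already use up all of 422.

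Third, the ventilator-free-days power claim might seem to fall with the precision claim. For an unadjusted comparison of independent patients it does not. With 25% prevalence and 380 analysed (95 v 285), a 3-day difference and SD 9, the standard error is 9 × √(1/95 + 1/285) = 1.066, and a t-test has power of about 80.1%. That confirms the stated minimum of 80%. No error is claimed there.

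**Conclusion.** The precision statement is wrong as written: 422 is an independent-patient sample size for a design that samples patients within ICUs, in a plan that recognises centre correlation elsewhere. At 50% prevalence and 10% loss the half-width is 5.03 points before any clustering, which by itself is a rounding matter, and every positive ICC adds to it.

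The size cannot be fixed from the article. Over the assumed range of 4 to 20 patients per ICU and ICC 0.01 to 0.10, with 380 analysed, the half-width runs from about 5.1 to 8.6 points; 6.05 to 6.9 corresponds to 10 per ICU and ICC 0.05 to 0.10. With all 422 analysed, or a prevalence well away from 50%, the shortfall shrinks and can vanish at a low ICC. Coverage of about 90% or 85% (40 equal ICUs, ICC 0.05 or 0.10) applies only if a plain binomial interval is used. The point estimate, the design and the ventilator-free-days model are unaffected.

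**What to change.** - Keep 422 patients. In the sample size section, state that the figure assumes independent patients, and give the expected half-width over a stated range of ICC and patients per ICU, as in the table above.
- In the statistical section, specify that the confidence intervals for the prevalence and the other proportions are computed with ICU as the cluster, by a cluster-robust variance or a bootstrap that resamples ICUs.
- Report the estimated ICC with the prevalence.

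Stratifying the variance by country is not required: ICUs come by network and snowball invitation, the number per country is not given, and a stratum with a single ICU would leave the stratified variance undefined.

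The cost is a few sentences and a routine analysis in R, with no extra patients or data. The only downside is a less favourable stated precision and wider intervals.

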### Study measures and data collection

The following baseline characteristics related to admission to the ICU and initiation of MV will be obtained from the patient's medical records: age, sex, height (assessed using a tape measure with the patient in the supine position), weight reported by the ICU team, main reason for admission to the ICU, cause of ARF, arterial oxygen pressure/fraction of inspired oxygen ratio (PaO_2_/FiO_2_) on the day of the ARF diagnosis, date of intubation, risk factors for ARDS, comorbidities (cardiac, respiratory, neurological, renal, hepatic, immunosuppression, cancer, arterial hypertension, diabetes and smoking) and Simplified Acute Physiology Score 3 (SAPS 3). We will calculate the PBW according to the following formulas:

$$\begin{array}{c} 50+0.91\times \left(\text{height in centimeters}-\;152.4\right)\text{for males}\\ 45.5+0.91\times \left(\text{height in centimeters}-\;152.4\right)\text{for females} \end{array}$$

We will also retrospectively collect the ventilatory parameters from the day before inclusion in the study from the patient's medical records, in addition to the use of vasopressors, sedatives, neuromuscular blockers and analgesics, ARDS diagnosis, Richmond Agitation-Sedation Scale (RASS) score, presence of *delirium* assessed by the Confusion Assessment Method in an Intensive Care Unit (CAM-ICU) scale or clinical assessment, Sepsis-related Organ Failure (SOFA) score, blood gas analysis and other laboratory data for diagnosing organ failure. We will also calculate the respiratory system compliance and resistance from the day before study enrollment (for patients under deep sedation and/or neuromuscular blockage). The main study measures and data collection methods are shown in table 2.

**Table 2 t2:** Characteristics of the study population

Characteristic		Value
Age (years)		xx ± x
Male, n (%)		n (xx)
BMI (kg/m^2^)		xx ± x
SAPS 3 score		xx ± x
SOFA		xx (xx - xx)
LIP score		xx (xx - xx)
Charlson index		xx (xx - xx)
Cause ARF		
	Pneumonia (bacterial, viral, opportunistic)	n (xx)
	Extrapulmonary sepsis	n (xx)
	Coma/lowered level of consciousness	n (xx)
	Cardiogenic pulmonary edema/heart failure	n (xx)
	Aspiration	n (xx)
	Hypovolemic shock	n (xx)
	Others	n (xx)
Days of intubation prior to inclusion		xx (xx - xx)
Cause of hospitalization		
	Acute respiratory failure	n (xx)
	Sepsis	n (xx)
	Neurologic diseases	n (xx)
	Postoperative monitoring	n (xx)
PaO_2_/FiO_2_ ratio at ARF diagnosis		xx ± x
Duration of invasive MV (days)		xx (xx - xx)
Mechanical ventilation-free days (days)		xx (xx - xx)
Duration of ICU stay (days)		xx (xx - xx)
ICU survival, n (%) [95%CI]		n (xx) (xx- xx)
Duration of hospital stay (days)		xx (xx - xx)
Hospital survival, n (%) [95%CI]		n (xx) (xx- xx)

BMI - body mass index; SAPS3 - Simplified Acute Physiology Score 3; SOFA - Sequential Organ Failure Assessment; LIP - lung injury prediction; ARF - acute respiratory failure; PaO_2_/FiO_2_ - partial oxygen pressure/fraction of inspired oxygen; MV - mechanical ventilation; IQR - interquartile rage; ICU - intensive care unit. The data are expressed as the mean ± standard deviation, n (%), median (interquartile range) or n (%) (95%CI).

